### Eligibility criteria

#### Subjects living with migraine

##### Inclusion criteria

Adults between 25 and 55 years of age of both sexes;European descent;Diagnosis of HFEM (patients fulfilling the diagnostic criteria for migraine with or without aura and experiencing 8–14 monthly headache days during the previous 3 months) or CM (≥15 headache days migraine/month, of which 8 have migraine characteristics for at least 12 months) according to the International Classification of Headache Disorders, 3rd edition (ICHD-3, 31).

##### Exclusion criteria

a headache frequency of more than 25 days/month in the last 3 months;presence of acute medication overuse according to ICHD-3 criteria in the 3 months prior to the enrolment;any other significant medical condition (including neurological disorders, severe psychiatric illness, or cardiovascular disease);history or evidence of drug, or alcohol abuse or dependence within 12 months before the baseline visit;pregnant or breastfeeding women;women of childbearing potential (defined as all women physiologically capable of becoming pregnant) not using a reliable contraceptive method;concomitant use of other migraine preventive drugs.

#### Healthy controls

Adults between 25 and 55 years of age of both sexes;European descent;Absence of any personal or first-degree familial history of recurrent primary or secondary headache disorders;Absence of any other significant medical condition (including neurological disorders, severe psychiatric illness, or cardiovascular disease);Absence of any history or evidence of drug, smoking, or alcohol abuse or dependence within 12 months before the baseline visit.

Pregnant or breastfeeding women were not included in this study.

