### Subjects recruitment

Participants were recruited in three tertiary headache centres: C. Mondino Foundation in Pavia (Italy), Vall d’Hebron University Hospital/Vall d’Hebron Institut de Recerca (VHIR) in Barcelona (Spain) and Institut für Systemische Neurowissenschaften, Universitätsklinikum Hamburg-Eppendorf Hamburg (Germany).

Each centre enrolled a group of patients with HFEM or CM and a group of age- and sex-matched healthy subjects.

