### Interventions

#### Subjects living with HFEM or CM

They are assessed at baseline, then they receive a 3-month course of treatment with erenumab, a mAb targeting the CGRP receptor. The choice to use erenumab was dictated by the fact that it was the first and, at the time the trial began, the only CGRP-targeting mAb available on the European market.

No concomitant migraine preventive treatment was allowed during the screening, baseline and the 3-month treatment period. Abortive medications were allowed, but the type and formulation had to be the same throughout the study. Their usage was registered as well.

Their responders/non-responder status was defined assessed at the end of the 3-month treatment cycle, based on the headache diary data. Patients were classified as responders (R) if they achieved a ≥50% reduction in monthly headache days (MHD) during the final 4 weeks of the 12-week erenumab treatment period compared with the 4-week baseline run-in period. Patients who achieve a <50% reduction in MHD were classified as non-responders (NR). Within the R group, super responders (SR) were defined as patients who achieve a ≥ 75% reduction in MHD over the same period. Within the NR group, full non-responders (FNR) were defined as patients who achieve a < 25% reduction in MHD over the same period.

At visit 1, inclusion/exclusion criteria were reviewed; demographics and clinical characteristics were recorded. To avoid sample heterogeneity and to identify and minimise confounding factors, all participants underwent a structured interview to collect demographic information, including age, sex, ethnicity; clinical information including habits of caffeine, tobacco and drug consumption, physical activity level; life-time comorbidities, medication use, menstrual status and migraine-related information.

At this visit, participants started recording their headache characteristics in an *ad hoc* diary for a month to confirm the diagnosis at the following visit.

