### Statistical analysis

#### Efficacy endpoint analyses

The primary objective of the study is to identify a panel of biomarkers that is reliably associated with response to treatment in a substantial proportion of patients with migraine. To this end, we will develop classification algorithms that assign patients to response categories defined on an ordinal scale. Supervised machine-learning approaches based on parametric, semi-parametric and non-parametric models are going to be fitted and compared. The optimal model will be selected according to predefined performance criteria, including area under the curve (AUC), accuracy, precision and recall.

Secondary analyses will characterise differences between migraine patients and healthy controls at baseline in: (i) DNA methylation profiles; (ii) structural and functional magnetic resonance imaging measures; and (iii) pharmacogenetic, biochemical, clinical and psychological variables. Within the migraine cohort, we will also compare DNA methylation, brain morphometry and functional connectivity, as well as pharmacogenetic, biochemical, clinical and psychological measures, among patients classified as responders and non-responders to CGRP-targeting mABs.

Given the prospective design, changes in clinical status, disability and psychometric measures, from baseline to the end of the treatment period, are going to be evaluated to quantify the impact of the therapy and to relate these changes to treatment response categories. In parallel, longitudinal differences in structural and functional magnetic resonance imaging measures among response groups are going to be examined to identify treatment-related brain changes and estimate their effect sizes in relation to drug exposure and clinical improvement (e.g., reduction in monthly headache days).

Finally, plasma concentrations of CGRP, IL-1β and TNF-*α*, together with their messenger RNA expression in peripheral blood mononuclear cells, are going to be assessed over the course of treatment to explore treatment-related alterations in peripheral inflammation and their correlation with clinical endpoints, including headache frequency, acute medication intake and disability.

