#### Descriptive and inferential statistics

All computations were conducted via *R* software (version 4.4.0). Quantitative variables were compared using the cross-sectional Mann–Whitney test, whereas categorical variables were assessed via the chi-square test or Fisher’s exact test. A value of *p* < 0.05 was considered statistically significant. The statistical plan included baseline comparisons between R and NR across clinical, anamnestic, psychological, and disability measures. Variables were also compared between healthy controls and migraine patients, stratified for gender and diagnosis. Predictive thresholds for circulating serum *α*-CGRP, IL-1β, and TNF-α levels were estimated in patients using binomial logistic regression (generalised linear model, GLM).

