#### Mitigation of confounding factors

Given the real-world observational design of the BIOMIGA study, several measures were adopted to minimise the influence of potential confounding factors. Clinical outcome classification were based on prospectively collected headache diaries, which represent the reference standard for the assessment of migraine outcomes in real-world studies and reduce recall bias through systematic longitudinal recording of headache frequency and acute medication use (39). Standardised eligibility criteria limited major sources of confounding, including medication overuse headache, concomitant preventive treatments, severe neurological or psychiatric disorders, cardiovascular diseases, substance abuse, and other medical conditions potentially affecting biomarker levels or treatment response.

Demographic and clinical variables, including age, sex, migraine subtype, disease duration, baseline monthly migraine days, disability measures, acute medication intake, and relevant comorbidities, were systematically collected and evaluated as potential confounders. Analyses aimed at identifying clinically meaningful cut-offs for circulating CGRP concentrations were performed using GLM for prespecified clinical and demographic covariates to estimate independent associations while accounting for potential confounding. For epigenetic analyses, standardised procedures were adopted to minimise pre-analytical variability. Quality-control procedures and batch-effect correction methods were applied where appropriate, and known determinants of DNA methylation variability, including age, sex, medication exposure, and lifestyle-related factors such as smoking habits, were considered during statistical analyses to reduce potential confounding.

To reduce variability in neuroimaging-derived measures, MRI data were acquired using standardised acquisition protocols and processed through harmonised quality-control and preprocessing pipelines. Structural and functional MRI datasets underwent visual and automated quality assessment, with exclusion of scans affected by major artefacts or excessive motion.

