Established preprocessing procedures, including motion correction, spatial normalisation, and nuisance signal regression for functional MRI data, were applied to minimise non-biological sources of variability. In addition, demographic and imaging-related factors known to influence brain measures, such as age, sex, and head motion parameters, are going to be considered during statistical modelling and feature selection procedures.

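### Smoking abuse or dependence excludes healthy controls but, as written, not patients, so the secondary patient-versus-control comparisons may be confounded by smoking

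*Protocol article*

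**What the plan says.** The two eligibility lists treat smoking differently. Under Healthy controls, the Protocol article requires "Absence of any history or evidence of drug, smoking, or alcohol abuse or dependence within 12 months before the baseline visit". Under Exclusion criteria for subjects living with migraine, the corresponding item is "history or evidence of drug, or alcohol abuse or dependence within 12 months before the baseline visit"; smoking does not appear in it.

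Under Subjects recruitment, each centre enrols patients and "a group of age- and sex-matched healthy subjects". Smoking is not a matching factor.

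Tobacco use is recorded. The structured interview, described for all participants under visit 1, collects "clinical information including habits of caffeine, tobacco and drug consumption".

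On the analysis:
- Efficacy endpoint analyses: "Secondary analyses will characterise differences between migraine patients and healthy controls at baseline", covering methylation, MRI, and pharmacogenetic, biochemical, clinical and psychological variables.
- Descriptive and inferential statistics: quantitative variables are compared by Mann–Whitney and categorical ones by chi-square or Fisher tests. The section adds: "Variables were also compared between healthy controls and migraine patients, stratified for gender and diagnosis".
- Mitigation of confounding factors, epigenetic analyses: "lifestyle-related factors such as smoking habits, were considered during statistical analyses to reduce potential confounding".
- Imaging: scanner site is a covariate in all group-level analyses (Acquisition protocol), and factors "such as age, sex, and head motion parameters, are going to be considered during statistical modelling".

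**The concern.** If the lists are applied as printed, smoking dependence is possible among patients and absent among controls by design. A marker that responds to smoking can then differ between the groups with no migraine effect at all. The article itself names smoking habits as a known determinant of methylation variability. Its section on confounding relies on standardised eligibility criteria to limit confounding by substance abuse; for smoking, those criteria would create the imbalance.

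At stake are the secondary patient-versus-control contrasts. The Strengths section presents the control group as the reference that separates disease-specific signals from background variability. For a smoking-sensitive marker, that separation is not secured by an unadjusted test stratified only by gender and diagnosis.

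**Working it through.** The plan gives no figure to reproduce here, so the check has two parts: what each modality's analysis names, and how large the bias could be.

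**What is named, by modality**
- CGRP and cytokines: unadjusted tests, stratified by gender and diagnosis. Smoking is not named. The logistic models for thresholds are fitted in patients and do not address the control comparison.
- MRI: site, and as examples age, sex and head motion. Smoking is not named.
- Methylation: smoking habits are named. The form of the covariate is not given.

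**Inputs for the illustration**
- 168 patients and 51 controls (Sample size calculation; required minimums, not enrolled numbers).
- Assumed, because the documents give neither: proportion p of patients with smoking dependence, 10% to 30%, with 0% in controls; effect b of dependence on a marker, 0.3 to 1.0 SD. There is no true migraine effect.

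**Unadjusted comparison**

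Bias = p × b. SE = √[(1 + p(1 − p)b²)/168 + 1/51]. Type I error = Φ(−1.96 + bias/SE) + Φ(−1.96 − bias/SE). This is a normal approximation for means; the planned test is rank-based, so the figures are indicative.

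Worked case, p = 0.20 and b = 1.0: bias = 0.20; SE = √(1.16/168 + 1/51) = 0.163; ratio = 1.23; type I error = 23%.

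| p | b (SD) | bias (SD) | type I error |
|---|---|---|---|
| 10% | 0.3 | 0.03 | 5.4% |
| 10% | 1.0 | 0.10 | 9.5% |
| 20% | 0.5 | 0.10 | 9.5% |
| 20% | 1.0 | 0.20 | 23% |
| 30% | 0.5 | 0.15 | 15% |
| 30% | 1.0 | 0.30 | 45% |

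**Adjustment or restriction**

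Suppose a dependence indicator is added to the model and no control is dependent. The group coefficient is then exactly the mean of non-dependent patients minus the mean of controls, which is the restricted comparison. In 4,000 simulated trials at p = 20% and b = 0.5, the mean bias fell from 0.095 SD to −0.005 SD under both methods, and the SE rose from 0.163 to 0.166 (1.8%). With a smoking effect 0.5 SD larger in patients, the bias fell from 0.198 to −0.003 SD.

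Ignoring the smoking variance, removing 20% of patients (168 to 134) changes the SE by √(1/134 + 1/51) / √(1/168 + 1/51) = 0.1645/0.1599 = 1.029.

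**A crude yes/no smoker covariate**

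Assume 20% dependent patients, 10% light smokers in both groups, and effects of 0.8 and 0.2 SD.
- Unadjusted bias: 0.2 × 0.8 + 0.1 × 0.2 − 0.1 × 0.2 = 0.16 SD.
- Among smokers, the patient mean is (0.16 + 0.02)/0.30 = 0.6 and the control mean is 0.2, a gap of 0.4. Among non-smokers the gap is 0.
- Regression weights n₁n₂/(n₁ + n₂): smokers 50.4 × 5.1/55.5 = 4.63; non-smokers 117.6 × 45.9/163.5 = 33.0.
- Residual bias: 0.4 × 4.63/(4.63 + 33.0) = 0.05 SD. The simulation gave 0.050, and 0.001 when dependence was coded as a separate level.

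**The case against.** Much of the case on the other side is sound.

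- **Drafting slip.** The patient item has a stray comma where the control item has the word smoking, and the two are otherwise parallel. A dropped word is plausible. This stands as a possibility, which is why clarification comes first; the text as printed does not exclude dependent smokers from the patient group.
- **Scope of the unadjusted tests.** The sentence before the control comparison lists clinical, anamnestic, psychological and disability measures, and methylation and MRI have their own covariate statements. This stands: those two modalities should not be read as planned unadjusted rank tests. CGRP and cytokines have no such statement for the control comparison.
- **Left to the full plan.** The imaging covariates are given as examples, and an article may leave complete lists elsewhere. This weakens the MRI part. It does not remove the printed difference in selection, to which no named remedy corresponds outside methylation.
- **Adjustment useless.** A reader might infer that, with no dependent smokers among controls, the groups do not overlap and adjustment is mere extrapolation. The documents do not support that. The control criterion bars abuse or dependence, not all smoking, so the groups overlap among non-dependent participants, and a dependence indicator gives the same estimate as restriction. Only the contrast among dependent smokers lacks controls.
- **Small effect.** At 10% dependence and 0.3 SD the error rate is almost nominal. This stands as the lower end of the range.

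**Conclusion.** The point holds as a risk to the secondary patient-versus-control comparisons. It is strongest for CGRP and cytokines and weaker for MRI. For methylation it is limited to the chance that a crude covariate leaves residual bias. Its size cannot be determined from the document: over the assumed ranges it runs from negligible (0.03 SD, 5.4% error) to serious (0.30 SD, 45% error). A reader might take these comparisons to be confounded as a fact; the smoking rates and effects needed to say so are not given.

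A reader might also extend the concern to the primary objective. That does not follow, because responder status is compared within patients and the controls play no part. The remedy is inexpensive and the comparisons are secondary, so this should be corrected but does not threaten the main result.

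**What to change.** 1. Reconcile the two eligibility lists by stating whether the smoking criterion also applied to patients.
2. If it did not, adjust the CGRP/cytokine, MRI and methylation patient-versus-control comparisons for recorded tobacco use, graded by intensity where the data allow rather than coded yes/no.
3. Also report each of these comparisons restricted to patients who meet the controls' smoking criterion, as far as the recorded data permit that classification.
4. Leave the responder versus non-responder analyses on all patients.

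Recruitment is closed, so only the analysis and its wording can change. The standard error rises by about 2–3% if 20% of patients are removed, and the restricted contrast then applies to people without smoking dependence.

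Two points about the data need checking first. The article describes recording tobacco habits but no dependence measure. The interview is placed at visit 1 while controls attend only visit 2, although Table 1 marks history-taking for them. Baseline data are in their last round of revision according to Status of the study, so the wording should be settled before that closes.

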### Interventions

#### Subjects living with HFEM or CM

They are assessed at baseline, then they receive a 3-month course of treatment with erenumab, a mAb targeting the CGRP receptor. The choice to use erenumab was dictated by the fact that it was the first and, at the time the trial began, the only CGRP-targeting mAb available on the European market.

No concomitant migraine preventive treatment was allowed during the screening, baseline and the 3-month treatment period. Abortive medications were allowed, but the type and formulation had to be the same throughout the study. Their usage was registered as well.

Their responders/non-responder status was defined assessed at the end of the 3-month treatment cycle, based on the headache diary data. Patients were classified as responders (R) if they achieved a ≥50% reduction in monthly headache days (MHD) during the final 4 weeks of the 12-week erenumab treatment period compared with the 4-week baseline run-in period. Patients who achieve a <50% reduction in MHD were classified as non-responders (NR). Within the R group, super responders (SR) were defined as patients who achieve a ≥ 75% reduction in MHD over the same period. Within the NR group, full non-responders (FNR) were defined as patients who achieve a < 25% reduction in MHD over the same period.

At visit 1, inclusion/exclusion criteria were reviewed; demographics and clinical characteristics were recorded. To avoid sample heterogeneity and to identify and minimise confounding factors, all participants underwent a structured interview to collect demographic information, including age, sex, ethnicity; clinical information including habits of caffeine, tobacco and drug consumption, physical activity level; life-time comorbidities, medication use, menstrual status and migraine-related information.

At this visit, participants started recording their headache characteristics in an *ad hoc* diary for a month to confirm the diagnosis at the following visit.

At visit 2, participants performed the following procedures:Diagnosis confirmation based on data recorded in the diary;Assessment of migraine-related disability, psychometric variables, quality of life, comorbidities, acute medications intake and Emergency Room Use in the previous month;Venous blood samples for DNA extraction for DNA methylation analysis for CGRP-related polymorphisms, and for biochemical profiling;Neuroimaging evaluation: 3 T Magnetic resonance imaging (MRI), including structural, resting state MRI (rsMRI), Arterial Spin Labelling (ASL) using a standardised protocol provided by UKE.

Once the assessment was completed, participants were administered the first 140-mg dose of erenumab. Upon discharge, the patient received 2 additional 140-mg doses of the drug, a training on the modality of self-injection and the schedule for self-injection (one dose every 28 days).

Visits 3 and 4 were remotely conducted to collect data from diaries, clinical scales and verify that the patients managed to self-inject the drug properly.

At visit 5, participants under:Assessment of treatment efficacy through the headache diaries and stratification of based on the response to treatment;Assessment of treatment satisfaction with validated patient-reported outcomes (PROs, listed in Table 1 and detailed in the next paragraph);Assessment of migraine-related disability, psychometric variables, quality of life, comorbidities, acute medications intake and Emergency Room use in the previous month; Assessment of epigenetic, biomolecular and neuroimaging parameters only for the SR and FNR subgroups.

**Table 1 tab1:** Scheduled activities for subjects with migraine and healthy controls.

	Subjects living with migraine					Healthy subjects
	Baseline (4 wk)	Treatment period				All activities were performed at visit 2
	Day 0	Day 1	Wk + 4	Wk +8	Wk +12 End of observ	
Visit number	1	2	3*	4*	5	
Informed consent	X					X
Pregnancy test	X	X				
Headache diary explained and given to patient	X	X	X	X	X	
Headache diary data collected		X	X	X	X	
Demographics, medical & headache history	X					X
Physical and neurological examination & vital signs	X				X	X
Adverse events		X	X	X	X	
Concomitant medications	X	X	X	X	X	
Blood samples§	X				X**	X
Neuroimaging	X				X**	X
Dosing		X	X	X		
MIDAS		X			X	
HIT-6		X			X	
BAI		X	X	X	X	X
BDI-II		X	X	X	X	X
MIG-SCOG		X			X	
MSQ		X			X	
PGI-I		X	X	X	X	

* Remote visit; ** Only for super responders and full non-responders. MIDAS, Migraine Disability Assessment; HIT-6, Headache Impact Test-6; BDI-II, Beck Depression Inventory-II; BAI, Beck Anxiety Inventory; MSQ, Migraine-Specific Quality of Life Questionnaire; MIG-SCOG, Migraine-Specific Cognitive Impairment Scale; PGI-I, Patient Global Impression of Improvement. § Pharmacogenetic polymorphisms, plasma levels of CGRP and cytokines.

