However, only a subset of patients achieve a ≥ 50% or ≥75% reduction in migraine days with CGRP-pathway-targeted therapies, highlighting the need for precision medicine approaches capable of matching individuals to the most effective therapy (11). Central to such approaches is the identification of robust biomarkers that can predict the likelihood of response. Despite decades of investigation, no biomarker has yet been validated for routine clinical use in migraine, either for diagnosis, disease staging, or prediction of treatment response (12, 13).

Multiple classes of candidate biomarkers have been explored. Circulating peptide markers, including CGRP and related neuropeptides, show increases during spontaneous and induced attacks and correlate with headache frequency and acute medication intake, but inter-individual variability, methodological differences and overlapping values with controls have limited their clinical utility (14, 15). Peripheral microRNAs show changes in chronic migraine and medication overuse and may normalise after detoxification or anti CGRP preventative therapy, but findings remain inconsistent and based on small samples (16, 17). Integrated molecular models combining miRNA profiles and genetic risk score have recently shown high discriminative accuracy, supporting multi-omic approaches, but still lack proper accessibility (18). Neuroimaging studies have shown structural and functional changes in pain-processing networks. Multimodal MRI can differentiate between migraine patients and controls, although there are currently no reliable imaging predictors for predicting response to CGRP-targeted treatments (13, 19, 20). Single-nucleotide polymorphisms (SNPs) modestly contribute to the risk of migraines, while changes in methylation at CGRP-related loci may affect migraine chronicity and the response to treatment (21–23). Genome-wide methylation studies further support distinct epigenetic signatures in migraine, but their relationship with pharmacological response is still largely unexplored.

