Focusing on a single preventive agent, subcutaneous erenumab, at the dosagike of 140 mg, is also methodologically robust. Erenumab targets the CGRP receptor, has a well-characterised pharmacokinetic profile and has demonstrated consistent efficacy and safety in both episodic and CM, therefore gaining “strong in favour” endorsement in the International Headache Society (IHS) – Società Italiana Studio Cefalee (SISC) guidelines for migraine prevention (4). Concentrating on one mechanism-specific therapy reduces pharmacological heterogeneity and facilitates the attribution of biomarker patterns to a defined biological target. The prospective collection of longitudinal data, with repeated clinical, psychometric and imaging assessments, allows evaluation of within-person changes over time and supports analyses relating biomarker dynamics to clinical response, rather than relying solely on cross-sectional comparisons. Moreover, the inclusion of a control group provides an essential reference framework, enabling the differentiation of disease-specific signals from background biological variability and thereby strengthening the validity and interpretability of the findings.

Finally, BIOMIGA adopts advanced analytical ML strategies to identify prediction models that balance interpretability and performance. This structured approach, coupled with prespecified performance metrics and internal validation, is a strength in the context of high-dimensional biomarker research.

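### Response is scored against a single run-in month with no untreated migraine group, so chance variation in that month can make state-dependent baseline features look predictive, and the before-after change cannot measure drug impact

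*Protocol article*

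**What the plan says.** Under Interventions (Subjects living with HFEM or CM), a responder has at least a 50% reduction in monthly headache days "during the final 4 weeks of the 12-week erenumab treatment period" "compared with the 4-week baseline run-in period". Super responders need at least 75%, and "full non-responders (FNR) were defined as patients who achieve a < 25% reduction in MHD over the same period".

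The run-in diary has a second use: visit 2 lists "Diagnosis confirmation based on data recorded in the diary". Entry also rests on history, since HFEM means "experiencing 8–14 monthly headache days during the previous 3 months", and patients above 25 days a month over the last 3 months are excluded.

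The visit 2 text places disability and psychometric scales, previous-month acute drug use, blood sampling and MRI before the first dose. Table 1 marks blood and neuroimaging at visit 1. All migraine patients are treated. Healthy controls are assessed once.

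On analysis:
- Descriptive and inferential statistics compares responders with non-responders by Mann–Whitney, chi-square or Fisher tests.
- Preprocessing and feature selection screens candidates one at a time against response.
- Mitigation of confounding factors lists baseline monthly migraine days among the potential confounders. It says the CGRP cut-off models use prespecified covariates.
- Efficacy endpoint analyses says changes in clinical status, disability and psychometric scores "from baseline to the end of the treatment period, are going to be evaluated to quantify the impact of the therapy".

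**The concern.** The run-in count is the denominator of the outcome. Any chance excess in that month inflates the apparent reduction, whatever the drug does, because later months tend to return to the patient's usual level. A baseline feature that shares the excess will then be associated with the response label.

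The article itself gives a reason to expect such features. Its Background says circulating peptides rise during attacks and "correlate with headache frequency and acute medication intake".

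No untreated or placebo migraine group shows how far patients would have drifted without the drug. Nested cross-validation does not help, because the shared error is present in every fold. At stake is whether a state-dependent member of the panel reflects sensitivity to erenumab or only a bad run-in month, and whether the mean before-after change can be called a drug effect.

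**Working it through.** The article gives no figure on this point, so there is none to reproduce. The definitions and entry limits below come from the article. The variability and correlation values are assumptions.

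**Mechanism.** Let T be a patient's usual monthly headache days, d the chance deviation in the run-in month, and F the count in the final 4 weeks. The measured reduction is 1 − F/(T + d). Take T = 15, a true cut of 50% (expected F = 7.5) and d equal to one assumed monthly SD of 3 days:
- d = 0: 1 − 7.5/15 = 50.0%
- d = +3: 1 − 7.5/18 = 58.3%, a responder
- d = −3: 1 − 7.5/12 = 37.5%, a non-responder

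The drug effect is the same in all three cases, and only the run-in month decides the label.

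**Simulation A: drug effect varies but is independent of everything else.** Assumed: T has mean 15 and SD 4.5; monthly SD 3 (range 2 to 4); 3-month history = T plus error of SD/√3; entry on history 8 to 25 and run-in at least 8; individual reduction drawn from Beta(1.6, 1.6); 600,000 patients per setting.

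Responder rate from the lowest to the highest tertile of d:
- monthly SD 2: 43% to 61%
- monthly SD 3: 41% to 65%
- monthly SD 4: 40% to 69%

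Repeat runs at SD 3 gave 63% to 66% in the top tertile.

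Odds ratio of response per SD of a marker with no relation to drug effect:
- Correlation 0.5 with d: 1.25 (1.18 to 1.31 over monthly SD 2 to 4; 1.23 in a repeat run). Adjusting for run-in days alone leaves about 1.17. Adding an accurate 3-month history leaves about 1.07. If that history carries recall error of SD 2 to 4 days, 1.10 to 1.15 remains.
- Correlation 0.2 with d: about 1.10 (1.06 to 1.09 in a repeat run).
- Correlation 0.5 with observed run-in frequency: about 1.11 (1.09 in a repeat run), and 1.00 after adjusting for run-in days.
- Correlation 0.5 with usual frequency T: 0.95 to 0.98, slightly the other way.

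**Simulation B: every patient has the same 50% cut, so no true differential response exists.** Assumed: mean T of 10 or 14 days before selection; between-person SD 5; month-to-month intraclass correlation 0.5 to 0.85; marker correlated 0.3 to 0.5 with d. The evaluable number is about 158, from the article's 168 and 6% loss (168 × 0.94 = 157.9).
- Responders and non-responders differ on the null marker by 0.18 to 0.35 SD. This reaches p < 0.05 in roughly 20% to 58% of studies instead of 5%.
- Super responders and full non-responders differ by 0.29 to 0.73 SD.
- With a 3-month mean as baseline and correlation 0.5, the first difference falls from 0.30–0.35 to 0.12–0.13 SD, and the second from 0.45–0.73 to 0.18–0.28 SD.

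**Selection alone, with no drug effect.** Under the assumptions of B, mean headache days fall by about 0.1 to 1.3 days, and 1% to 17% of patients are labelled responders.

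**The case against.** The strongest reply is that much of this is already handled or admitted. Baseline migraine days are a listed confounder, and the CGRP cut-off models are adjusted. The random-forest models add genetic, epigenetic and MRI data on top of a clinical block. Limitations and future directions concedes the open-label, non-randomised design and explains why there is no placebo arm. The models are called exploratory throughout.

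This stands in part, and a claim that the plan ignores baseline frequency would be wrong. But the responder tests and the univariate screen are stated without adjustment. The first random-forest block holds clinical and biochemical variables together, so plasma markers are not judged on top of clinical ones. The listed confounder is migraine days, whereas the label is built on headache days. Misclassification is discussed only for late responders, and regression to the mean is not named.

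A reader might also infer several stronger things that the document does not support:
- That plasma CGRP tracks the chance part of the run-in month. The Background speaks only of correlation with headache frequency. The correlation of 0.5 with the deviation is an assumption, and it drives the largest figure.
- That blood and MRI were certainly taken at the end of the run-in. The visit 2 text and Table 1 disagree. Interictal sampling, with drug-free intervals, may weaken the link further.
- That the Strengths section claims separation from placebo response. Its statement that using one drug "facilitates the attribution of biomarker patterns to a defined biological target" contrasts one agent with several.
- That a numeric 3-month frequency is on file for everyone. Eligibility needs a range, and no passage says a count was captured.
- That the eligibility cut greatly inflates the mean change. The 3-month history and the upper limit of 25 days restrain it.

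**Conclusion.** The concern holds in a limited form. With a single-month denominator and no untreated migraine group, chance variation in the run-in can give state-dependent features a false association with response. The features at risk are run-in frequency, previous-month disability and acute drug use, and possibly plasma CGRP, cytokines and functional MRI. Germline SNPs are not affected.

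The bias ranges from small to material: an odds ratio of about 1.10 to 1.25 per SD, depending on how closely a marker follows the month's deviation and on month-to-month variability, neither of which the document gives. If a marker follows only observed run-in frequency, adjusting for that frequency removes the bias. If it follows the deviation itself, such adjustment removes only part.

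Separately, an uncontrolled before-after change mixes drug effect, placebo response and natural fluctuation, so it cannot quantify the impact of therapy. Neither point shows that the panel as a whole is an artefact.

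**What to change.** 1. Adjust every responder/non-responder and super-responder/full-non-responder biomarker comparison for run-in headache days. Add pre-enrolment 3-month frequency where a numeric value was recorded. Call a state-dependent biomarker a candidate predictor only if it adds to these, and state that recall error in the history leaves some residual bias.
2. Where that history exists, add a sensitivity analysis with the response label computed from the average of history and run-in. Keep the diary-based label as primary. In simulation A the averaged label brings the null odds ratio for the deviation-linked marker to about 1.06.
3. In Efficacy endpoint analyses, say that the before-after analyses describe change during treatment. In Limitations and future directions, state that the panel is associated with improvement during erenumab and cannot be separated from placebo response, natural fluctuation or regression to the mean.
4. Reconcile the visit 2 text and Table 1 on when baseline blood and MRI were taken.

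The cost is one or two covariates, one sensitivity analysis and some wording, with no new patients or visits. Status of the study says the analysis of stratified groups is still under way, so the changes can be made now. The price is a more modest claim and some noise from recalled history.
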